**Legend:**

( ), if applicable/optional

$x^1$ , monitoring for acute transfusion related toxicity while and up to 12 hours after CIK cell infusion, patients should be observed overnight within the context of an inpatient hospital stay. The study drug must be administered where emergency resuscitative equipment and personnel trained in the management of anaphylaxis are immediately available to treat systemic reactions under the direct supervision of a physician

$x^2$ , blood samples before, 1 hour, 1 and 2 weeks after CIK cell infusion for analyses of cytotoxic effects and tumor escape mechanisms

$x^3$ , monthly obligatory

$x^4$ , every 3 months

$x^5$ , optional

$x^6$ , once a year

$7$ , stop of CIK cell infusions: in case of molecular remission or if discontinuation criteria are reached,

If the patient does not reach molecular remission, administration of CIK cells will be stopped after the 8th CIK cell infusion.

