#### 4.1 Inclusion Criteria

- Acute leukemia and MDS patients with detectable MRD,  $\geq 10^{-4}$  of BCR-ABL/ABL ratio, or MC in PB or BM samples obtained during monitoring for relapse after allogeneic stem cell transplantation.
- Detectable MRD, or  $\geq 10^{-4}$  of BCR-ABL/ABL ratio .
- Acute leukemia and MDS patients with MC  $\geq 1\%$  of autologous signals in PB samples confirmed by another PB or BM sample within one week. Patients with MC  $\geq 1\%$  of autologous signals in CD33+ and/or CD34+ subpopulations in PB samples confirmed by BM analyses within one week. Acute leukemia and MDS patients with MC  $\geq 1\%$  of autologous signals including signals in CD33+ and/or CD34+ subpopulations in BM samples.
- Patients without immunosuppressive agents and steroids.
- Patients without chemo- or immune therapy, except patients with tyrosine-kinase inhibitors (TKI) for treatment of BCR-ABL positive leukemias.
- Patients with < grade II GvHD.
- Patients with Karnowsky or Lansky performance status  $\geq 50\%$ .
- Patients and/or his/her legal representative having reviewed the patient information/informed consent form and have had their questions answered and have given written informed consent.

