**The following criteria lead to stop of additional CIK cell infusions; patients are remaining in the study:**

- Development of GVHD > Grade II
- Response to CIK cell therapy: If mixed chimerism was the reason for study eligibility, than the achievement of complete donor chimerism leads to the stop of further CIK cell infusions. If the inclusion into the study was favored by minimal residual disease detection, the achievement of MRD negativity leads to a stop of additional CIK cell infusions.

- Severe infections

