## Analysis

A descriptive statistics will be performed at the end of the study. An intent-to-treat principle (ITT) or per-protocol analysis will be done.

To analyze the efficacy of CIK cell treatment following factors will be considered:

- Complete and partial molecular response
- rate and duration of complete/partial molecular response following CIK cell administration at the end of CIK cell infusions and after 1 year of first CIK cell infusion
- rate of and time to non response
- rate of and time to relapse with previous partial/complete response
- Progression-Free survival (PFS) and overall survival (OS)
- Cumulative incidences of: haematological relapse/progression, deaths without relapse/progression
- Cumulative incidence of aGVHD > grade II and extensive chronic GvHD
- Median and range for the number of CIK cell dose and for cumulative dose CIK cells/kg for all patients, children and adults

- Median and range for cumulative T cells/kg according donor type (MSD, MUD,MMFD) that patient requires in the study

Complete molecular response is defined as the molecular remission: the Minimal Residual Disease not detectable (MRD < 10^-6) and Mixed Chimerism MC < 1%.

Partial response is defined as no molecular remission but not haematological relapse. Non response is defined as haematological relapse without previous or complete response.

The median of PFS and OS time will be estimated. Kaplan-Meier estimates will be used to estimate PFS probability and OS probability. Log-rank test will be used as appropriate. For PFS will be considered as events: disease progression or relapse, death without relapse/progression and secondary neoplasm. For OS death from any cause will be considered an event.

Gray-Model will be used for cumulative incidences. Patients lost to follow-up without event will be censored at the date of their last follow up evaluation.

PFS, OS and cumulative incidences will be estimated after 1 year initiation of CIK cell therapy and after 1 year until the last CIK cell infusion.

If the data meet the necessary requirements, longitudinal analysis will be conducted to explore the improvement of hematologic and immune reconstitution of leucocyte, CD3-, CD4-, CD8-, CD56-, and CD14-positive cells until the first year after begin of the CIK cells therapy.

The dynamic of cytokine profile during cell infusion and tumor escape mechanisms following CIK cell infusion will exhibit in curves over the time.

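### A single unconfirmed assessment can establish complete molecular response, for mixed-chimerism entrants at the same 1% cut as entry, so the complete response rate at the end of infusions can be overstated

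*Protocol*

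**What the plan says.** **Definition of response (Protocol section 11, Analysis).** "Complete molecular response is defined as the molecular remission: the Minimal Residual Disease not detectable" (below 10^-6) "and Mixed Chimerism MC < 1" per cent. The two conditions are joined by *and*. No repeat sample or minimum duration is stated. "Partial response is defined as no molecular remission but not haematological relapse".

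**When it is analysed.** Response is listed as "rate and duration of complete/partial molecular response following CIK cell administration at the end of CIK cell infusions", and the same sentence adds a second time point, 1 year after the first infusion. The exploratory efficacy endpoint in section 11 uses that 1-year point for complete and partial response.

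**Entry (sections 3.2 and 4.1).** MC of at least 1% found in blood must be "of autologous signals in PB samples confirmed by another PB or BM sample within one week". One marrow sample is enough on the marrow route. Detectable MRD, or a BCR-ABL/ABL ratio of at least 10^-4, also qualifies, with no second sample asked for.

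**Readings.** Blood chimerism during treatment is "monthly obligatory" in the synopsis schedule. Marrow is taken every 3 months. Treatment runs to at most 8 infusions or one year. After the last infusion, section 3.2 makes blood chimerism obligatory within one month and then every three months, while marrow is optional.

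**Stopping (section 8.1).** For patients admitted on mixed chimerism, "the achievement of complete donor chimerism leads to the stop of further CIK cell infusions". For those admitted on MRD, MRD negativity does so. No confirmation is stated, and only the entry marker is named.

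**The concern.** For the blood chimerism route the protocol asks for two readings to call a patient at or above 1%, but a single assessment can call the same patient below 1%. There is no gap between the two cuts, so a patient whose true MC is stable just above 1% gets a fresh chance each month of reading below it. Reaching remission ends infusions, so the time point at the end of infusions tends to coincide with the favourable reading. Entry on one positive marrow sample adds regression to the mean.

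The MRD condition protects patients in whom both markers are measured. It does not help where no MRD marker exists: section 2.2 plans chimerism in all patients but Ig/TCR and BCR-ABL only in leukemia patients, and section 3.2 asks for MRD only if appropriate. For an MC entrant without such a marker, MC below 1% is the only part of the definition that can be read.

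At stake are the complete response rate at the end of infusions, the start date of a response and its duration. Complete response is the only category that requires molecular improvement, so it carries the activity signal towards the larger study that section 11 has in view. With a single arm, nothing offsets a bias in it.

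**Working it through.** **1. The plan's own figure.** Exact (Clopper-Pearson) limits at a rate of 0.4 are 0.249 to 0.567 for 16/40 (width 0.318) and 0.191 to 0.639 for 8/20 (width 0.448). Both agree with section 11. They refer to the combined complete/partial rate.

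**2. Which rate can move.** Take a patient without haematological relapse whose true MC stays at or above 1%.

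| Reading | Category | In combined rate? |
|---|---|---|
| All at or above 1% | Partial | Yes |
| One falsely below 1%, no MRD marker or MRD undetectable | Complete | Yes |

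The false reading changes the split, not the combined rate.

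**3. Chance for one patient.** The documents give neither the assay CV nor the distribution of MC at entry, so these are assumptions. With log-normal reading error and true level m (in %):

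- σ = √ln(1 + CV²)
- p = P(one reading < 1%) = Φ(−ln m / σ)
- P(at least one of k) = 1 − (1 − p)^k

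For m = 1.5 and CV = 25%: σ = 0.246 and p = Φ(−0.405/0.246) = 0.050. Eight readings give 1 − 0.950^8 ≈ 0.335. Two consecutive low readings within eight have probability 0.017.

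| True MC | CV | p | Any of 8 | Two consecutive in 8 |
|---|---|---|---|---|
| 1.25% | 25% | 0.182 | 80% | 19% |
| 1.5% | 25% | 0.050 | 33.5% | 1.7% |
| 3% | 25% | 0.000 | 0% | 0% |
| 3% | 50% | 0.010 | 7.7% | 0.1% |

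The effect is confined to patients close to 1%, unless the assay is very imprecise.

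**4. Across patients, no treatment effect, chimerism criterion only.** Simulation with true MC log-uniform on 0.3-5%, CV 15-35%, patients kept if their entry reading(s) are at least 1%, then nine monthly readings (up to 8 infusions and at most one year give about 8 to 12):

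| Entry | MC course | Any of 9 < 1% | Two consecutive < 1% |
|---|---|---|---|
| Two samples | constant | 10-25% | 4-9% |
| One sample | constant | 14-33% | 7-16% |
| Either | doubles every 2 months | about 0-5% | below 1% |

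Per 20 MC entrants on the two-sample route, 10-25% is 2 to 5 patients. How many of the 40 will enter this way is not given.

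**5. Wider inputs.** With log-normal true MC (median 1%, 2% or 5%, log-SD 1), CV 10-50%, constant level and eight readings, any-of-8 runs from about 1% to 40% after two-sample entry and 2% to 50% after one-sample entry. Two consecutive low readings give 0.4-15% and 0.8-25%. One reading at a fixed month 12 gives about 0.4-12% and 0.6-20%. If MC doubles every two months, any-of-8 is at most 6% and 12%, and the month-12 figure is about 0%.

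**The case against.** The strongest case against has five parts.

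- **The definition needs both markers.** This is right. A reader might infer that MC below 1% alone, or negative MRD alone, makes a complete responder. The text does not say so, and the simulations describe the chimerism criterion alone. They apply directly only where no MRD marker is available or MRD is already undetectable.
- **Partial response absorbs the error.** This is right for the combined rate. A reader might infer that the sized response rate is inflated or that each extra look adds responders. Neither follows, because anyone short of remission and without haematological relapse already counts.
- **The 1-year time point is fixed.** This is right. A single reading there is still subject to assay error, but the stopping rule does not select it. It does not repair the rate at the end of infusions or the response date.
- **The size is assumed.** This is right. The benefit-risk section (5.5) expects every untreated at-risk patient to relapse, and rising MC shrinks the effect to a few per cent. But it gives no speed, so slow or stable MC is not excluded.
- **Entry is not uniformly stricter.** This is right. Marrow chimerism, MRD and BCR-ABL entry need one sample, and the 1% cut applies to MC entrants only. Why blood entry is confirmed is not stated, so no motive should be read into it.

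Response is also a secondary endpoint in an explorative study, and planned reporting of duration and of relapse after response would expose some short-lived responses. A statistical analysis plan could add confirmation. The protocol, however, writes out the definition and leaves confirmation out of it.

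**Conclusion.** The point holds for complete response at the end of infusions and for the dating and duration of response, chiefly in patients entered on mixed chimerism without an MRD marker. It does not hold for the combined complete/partial rate, nor for the stopping rule's influence on the 1-year time point.

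Under constant MC and a CV of 15-35%, a false low chimerism reading occurs in about 10-25% of two-sample entrants and 14-33% of one-sample entrants. Confirmation lowers this to about 4-9% and 7-16%. If MC doubles every two months, the any-reading figure is about 0-5%. These figures illustrate the mechanism; they do not estimate the trial's bias. The correction is worth making because it is cheap and the arm has no comparator, but it does not undermine the design.

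**What to change.** In the response definition in section 11, Analysis:

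1. Report complete response separately from partial response at both time points.
2. For the chimerism criterion, call complete response confirmed when the next obligatory blood chimerism is also below 1%, and date it from the first of the two readings.
3. For MRD and BCR-ABL, use the next marrow where one is taken. Later marrow is optional, so patients without one should be labelled unconfirmed and not moved out of complete response, since that would demote genuine responders for lack of an optional sample.
4. Show the confirmed rate and the rate of all complete responses (confirmed plus unconfirmed) side by side.

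The cost is a few lines in the definition and one additional table. No new sample is needed, because blood chimerism is already obligatory during treatment and after the last infusion. The downside is a somewhat lower stated complete response rate.

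Separately, section 8.1 (entry marker only, no numerical chimerism cut) and section 11 (both markers, MC below 1%) must be reconciled, so that the event that ends infusions and the event counted as remission are clearly related. Which stopping rule applies is for the sponsor's clinicians; none is proposed here.

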### **Follow up after last CIK cell infusion:**

**Within one month and thereafter every three months:**

- History taking\*
- Physical examination\*
- Karnowsky/Lansky performance index\*
- Peripheral blood
  - Blood count\*
  - Bilirubin\*
  - Immune status (optional)
  - Chimerism\*
- Bone marrow (optional)
  - Morphology or histology

Chimerism, including subpopulations if appropriate  
MRD if appropriate  
BCR-ABL/ABL ratio if appropriate

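### Complete molecular response requires both undetectable MRD and chimerism below 1%, but patients enter on any one marker, so some cannot be documented as complete responders when their marker clears

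*Protocol*

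**What the plan says.** **Definition.** In section 11 (Analysis), "Complete molecular response is defined as the molecular remission: the Minimal Residual Disease not detectable", with a bound of 10^-6, joined to a second condition: "and Mixed Chimerism MC < 1" per cent. The next category is residual: "Partial response is defined as no molecular remission but not haematological relapse".

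**Entry.** Section 4.1 admits "Acute leukemia and MDS patients with detectable MRD", or a BCR-ABL/ABL ratio of at least 10^-4, "or MC in PB or BM samples obtained during monitoring for relapse after allogeneic stem cell transplantation". One marker suffices.

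**Assays planned.** Section 2.2 plans chimerism in all patients. It ties BCR-ABL/ABL and Ig/TCR rearrangement testing to leukemia patients. During treatment, section 3.2 has marrow every three months, with MRD and BCR-ABL only where appropriate. After the last infusion, the schedule of assessments and section 3.2 make marrow optional, and the entry there is again "MRD if appropriate".

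**Stopping for response.** Section 8.1 uses the marker that led to entry. For chimerism entrants, "the achievement of complete donor chimerism leads to the stop of further CIK cell infusions"; for MRD entrants, "the achievement of MRD negativity leads to a stop of additional CIK cell infusions". The schedule legend and sections 3, 3.1, 3.2 and 3.3 instead stop infusions at molecular remission, the term that section 11 ties to both markers.

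**The concern.** Molecular response is the first secondary endpoint in section 2.4. A definition that needs two markers, applied to patients who need only one to enter, makes the result depend on what could be measured as well as on what the treatment did. A patient can clear the only marker that was abnormal and still be counted as a partial response because the other was never assayed.

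This matters because partial response cannot carry the molecular question. It takes in anyone short of molecular remission without haematological relapse, and eligible patients are already in that state at entry, since section 3.1 requires blasts below 5%. Complete response is the only category that shows a molecular change, and it is the one whose definition cannot be applied to every patient. If the mix of diagnoses, and so of available markers, differs between children and adults, the separate estimates for the two groups will also differ for that reason.

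**Working it through.** **1. The plan's own figure.** The protocol states a 95% interval width of 0.318 for a response rate of 0.4 with 40 patients, and 0.448 with 20. The exact (Clopper-Pearson) interval for x of n has lower limit Beta(0.025; x, n-x+1) and upper limit Beta(0.975; x+1, n-x), as quantiles.
- 16/40: 0.2486 to 0.5667, width 0.3181.
- 8/20: 0.1912 to 0.6395, width 0.4483.

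Both reproduce. They refer to complete and partial response combined.

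**2. Patients traced through the text.**

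| Patient | Section 8.1 | Section 11 |
|---|---|---|
| MDS, entered on mixed chimerism, chimerism clears, no MRD assay | Stops for response | First condition cannot be documented; partial response |
| Leukemia, entered on MRD, chimerism below 1% throughout, MRD clears | Stops for response | Complete response |
| Leukemia, entered on MRD, MRD clears, chimerism still 1% or more | Stops for response | Partial response |
| Entered on BCR-ABL/ABL, ratio clears | Marker not named | Marker not named |

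Only the second row is classified the same way by both sections.

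**3. Timing.** Section 11 assesses response one year after the first infusion, and also at the end of infusions. Eight infusions span 7 intervals of 4 to 6 weeks: 7 x 4 = 28 to 7 x 6 = 42 weeks. On an uninterrupted schedule the one-year assessment therefore falls after the last infusion, when marrow is optional. The MRD half can be missing even for patients who have a marker.

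**4. What moves and what does not.** Let k patients move from complete to partial response because of the definition. The combined count is (CR - k) + (PR + k) = CR + PR, so it is unchanged. The complete response rate falls by k/n.

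**5. Size, on assumed values.** The protocol gives no marker overlap. Suppose 16 of 40 clear their qualifying marker (0.40 is the protocol's worked rate, not a forecast), and a fraction f of them lack or fail the other marker. Complete responses under section 11 are then 16 x (1 - f).

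| f | Complete response | Rate (95% interval) |
|---|---|---|
| 0 | 16/40 | 0.40 (0.249 to 0.567) |
| 12.5% | 14/40 | 0.35 (0.206 to 0.517) |
| 25% | 12/40 | 0.30 (0.166 to 0.465) |
| 50% | 8/40 | 0.20 (0.091 to 0.357) |

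In a group of 20 with 8 clearing, f = 25% gives 6/20 = 0.30 (0.119 to 0.543).

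The fraction f mixes two kinds of patient. Those who lack the other marker are affected by assay availability. Those who fail it have measured residual disease and are reasonably not complete responders. At f = 25%, four patients move; if two lack and two fail, availability accounts for 2/40 = 0.05 of the fall of 0.10.

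**The case against.** The strongest reply is that little turns on this. The study is explorative, its primary endpoints are GvHD, and the precision tables use the combined rate, which does not change. That is right, and it limits the point to the complete response rate, its duration and the complete/partial split. A reader might infer that responders in general are misclassified; step 4 shows that they are not.

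Second, BCR-ABL may be meant as a form of MRD: the schedule lists the two as alternatives. If so, the omission reduces to an unstated clearance limit for that marker. The limit is still needed, because entry is set at 10^-4 and the definition at 10^-6.

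Third, section 4.1 mentions MDS patients with detectable MRD, and section 3.1 has marrow every three months after infusions for efficacy. Neither closes the gap. No MRD assay is named for MDS, and section 3.2 and the schedule make marrow optional after the last infusion. An analyst could also treat unmeasured MRD as not detectable, but the text does not say so, and the two readings give different rates.

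Three stronger inferences are not supported.
- **Assay noise.** A reader might infer that one chance chimerism reading below 1% creates a complete response. Section 11 also demands undetectable MRD, so chimerism alone does not meet it, and the protocol gives no assay error from which to compute a rate.
- **Confirmation.** Blood chimerism must be confirmed at entry, and nothing is said for response. That is silence, which an analysis plan not seen here may fill. At entry, MRD, BCR-ABL and marrow chimerism need no confirmation either.
- **Compartment and threshold.** A patient enrolled on a CD34+ subset might seem to meet the chimerism condition at baseline, and complete donor chimerism might seem to differ from mixed chimerism below 1%. Sections 3.1, 3.2 and 4.1 count subpopulations as mixed chimerism at a 1% threshold, which allows a consistent reading of both.

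**Conclusion.** The point holds in a limited form. Applied as written, the definition leaves patients without an MRD marker unable to be documented as complete responders, and it does not name one of the three entry markers. This is a stated rule that gives a wrong result for an enrolled group, so it is more than detail left for later.

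The size depends on marker availability, which the protocol does not report. With 16 of 40 clearing the qualifying marker, the complete response rate would be 0.35, 0.30 or 0.20 instead of 0.40 if an eighth, a quarter or half of them lack or fail the other marker. The fall of 0.10 in the middle case is about a third of the interval width (0.10/0.318 = 0.31), but it is systematic, and only the part due to missing assays is an artefact. The combined rate and its precision tables stand.

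The stopping passages are a separate contradiction: section 8.1 uses the entry marker alone, while the schedule legend and sections 3 to 3.3 use molecular remission. They must be reconciled. Which stopping rule is right is not judged here.

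**What to change.** For the analysis endpoint only, redefine complete response in section 11 as clearance of the qualifying marker, with any other marker that was measured also negative and no haematological relapse. Clearance would be one of:
- MRD not detectable, for patients who entered on MRD;
- BCR-ABL/ABL below a limit that the protocol states, for patients who entered on that ratio;
- mixed chimerism below 1% in the compartment used for entry, for patients who entered on chimerism.

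Report the rate and duration by qualifying marker as well as overall, with the number of patients whose qualifying marker was not assessed at each time point. Separately, bring section 8.1 and the passages on molecular remission into agreement.

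The endpoint change is wording and needs no new samples. Its downside is that the overall rate becomes a composite across markers, and patients with more markers measured still have more to clear, which is why the breakdown is needed. It does not supply marrow results that remain optional after the last infusion.

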## 1.5 Clinical Data

Based on our pre-clinical data, we analyzed safety and feasibility of a sequential, dose escalating administration of *in vitro* expanded CIK cells in patients with hematological malignancies after allogeneic SCT.

Our experience of repetitive, dose-escalating CIK cell infusions include 14 leukemia patients with risk of relapse (n=11) or overt relapse (n=3) showing no signs of acute GvHD >grade I after allogeneic SCT.

Between August 11, 2011 and November 30, 2014 14 patients (<18 years of age, n=13, median age 9, range 1-17 years; >18 years of age, n=1, age 69 years) with hematological malignancies (AML, n=7; ALL, n=6; CML, n=1) received a total of 58 CIK cell infusions (median number 3, range 1-10 per patient) from matched unrelated (n=6) or haploidentical (n=8) stem cell donors at a minimum of 3 weeks after allogeneic SCT and an interval of 4-6 weeks between infusions (median follow up after 1st CIK cell infusion 213 days, range 56-802 days). 6 patients received CIK cell infusions based on minimal residual disease or chimerism status, 5 patients, most of whom were not in remission at the time of allogeneic SCT, were treated prophylactically, and 3 relapsed patients received CIK cell infusions with or without chemotherapy.

Clinical batches of CIK cells were generated from peripheral blood mononuclear cells of the original stem cell donors under good manufacturing practice-conditions in the presence of interferon $\gamma$ , anti-CD3 antibody, interleukin (IL)-2 and IL-15. Cellular composition of CIK cell infusions showed that CD19+ B cells, CD14+ monocytes and CD3+CD56+ natural killer (NK) cells were quantitatively depleted while conventional CD3+CD56 T cells and CD3+CD56+ T-NK cells made up the bulk of the CIK cell product. T cells, evenly distributed between the CD4+ and CD8+ compartment, were activated, which was shown by CD25+ expression and were mostly TCR $\alpha/\beta$  type.

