### **2.2 Secondary Objectives**

To assess the efficacy of CIK cell treatment based on:

- Reduction or disappearance of MRD
  - Achievement of complete donor chimerism,
  - Rate of and time to hematologic relapse in patients enrolled based on MRD and/or mixed chimerism
  - Progression-free and overall survival
- Molecular relapse will be assessed by STR and RT-PCR based chimerism analyses in all patients, by real time (RT)-PCR based BCR-ABL/ABL, or immunoglobulin (Ig)/T cell receptor (TCR) gene rearrangements in leukemia patients

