- CIK cell infusions will be given within a minimum of 4 and a maximum of 6 weeks between infusions provided that signs of acute GvHD (aGvHD) remained below grade II aGvHD. Second CIK cell dose will be  $5 \times 10^6$  CD3+CD56 CIK cells/kg in pediatric and adult patients. Third CIK cell infusion and all following infusions will include  $1 \times 10^7$  CD3+CD56 CIK cells/kg in pediatric and adult patients. CIK cell infusions will be administered until the patient reaches molecular remission, provided that patients develop no more than grade I aGvHD.

If the patient does not reach molecular remission, administration of CIK cell infusions will be stopped after the 8th CIK cell infusion, maximal duration of the study phase is one year.

(For "Criteria for Discontinuation of the Treatment or Premature Withdrawal of the Patient" please also see chapter 8.1).

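### Complete molecular response needs both MRD and chimerism to clear, but section 8.1 stops infusions on the qualifying marker alone, so patients stopped for response and complete responders are overlapping but not identical sets

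*Protocol*

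**What the plan says.** **Response definition.** Section 11, Analysis, equates complete molecular response with molecular remission and defines it as "the Minimal Residual Disease not detectable (MRD < 10 -6 ) and Mixed Chimerism MC < 1" (the last figure is a percentage). Partial response is any state short of molecular remission without haematological relapse.

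**Stopping for response, first rule.** Section 8.1 looks only at the reason for entry. For patients who entered on mixed chimerism, "the achievement of complete donor chimerism leads to the stop of further CIK cell infusions". For those who entered on MRD, "the achievement of MRD negativity leads to a stop of additional CIK cell infusions". Complete donor chimerism is given no numeric cut there.

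**Stopping for response, second rule.** Section 3.1: "CIK cell infusions will be administered until the patient reaches molecular remission". Section 3, section 3.3 and the legend of the assessment schedule also use molecular remission. The Synopsis, under duration of participation, has a third wording that sets complete remission beside molecular remission and does not define the former.

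**Markers.** Section 2.2: "Molecular relapse will be assessed by STR and RT-PCR based chimerism analyses in all patients". The same sentence restricts the BCR-ABL/ABL ratio and Ig/TCR rearrangements to leukemia patients. Section 3.2 asks for MRD on treatment only where appropriate, in the three-monthly marrow. The Synopsis inclusion criteria, section 1.1, section 3.2 and section 4.1 list BCR-ABL as an entry trigger separate from MRD.

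**The concern.** The protocol uses one term, molecular remission, both for the event that ends treatment and for the efficacy event. Section 8.1 then ends treatment on a different event. Two sites that each follow a stated rule could treat the same patient differently, and the tabulated complete-response rate would not describe the patients whose infusions ended because they responded.

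The joint definition also needs an MRD result that some eligible patients cannot supply. Without a rule for them, the analyst decides after seeing the data whether such a patient can never be a complete responder or needs only the chimerism half. At stake are the complete-response rate, the complete/partial split and the interpretation of exposure (number of infusions and cumulative dose).

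**Working it through.** **1. The plan's own figures.** Section 11 gives 95% interval widths for the complete/partial molecular response rate. Exact (Clopper-Pearson) limits are: lower = Beta quantile at 0.025 with parameters x and n-x+1; upper = Beta quantile at 0.975 with parameters x+1 and n-x.
- 16/40: 0.2486 to 0.5667, width 0.3181 (plan: 0.318).
- 8/20: 0.1912 to 0.6395, width 0.4483 (plan: 0.448).

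Both are reproduced. They concern complete and partial response combined.

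**2. The rules side by side**

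| Patient | Section 8.1 | Section 3.1 read with section 11 | Section 11 response |
|---|---|---|---|
| Entered on MRD; MRD now negative, MC still 1% or more | stopped for response | endpoint not reached | partial |
| Entered on MC; complete donor chimerism, MRD still detectable | stopped for response | endpoint not reached | partial |
| Entered on MC; MC below 1%, MRD not detectable | depends on the unstated cut for complete donor chimerism | endpoint reached | complete |
| MDS, entered on MC; complete donor chimerism, no MRD assay | stopped for response | cannot be decided | cannot be decided |
| Entered on BCR-ABL/ABL; ratio has cleared | marker not named | marker not named | marker not named |

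The first two rows assume no haematological relapse. They show patients stopped for response who are not complete responders. The third row shows that the reverse is possible if complete donor chimerism is read more strictly than MC below 1%. Section 3.1 refers to section 8.1 but does not say which wording governs.

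**3. What does not move.** Suppose k patients fail the joint definition without haematological relapse. Complete responders fall by k and partial responders rise by k, so the sum is unchanged. The interval tables in section 11 therefore stand. The GvHD primary endpoints use neither marker.

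**4. What does move, under an assumption.** The documents give no discordance rate. Assume 16 of 40 patients (40%) stop for response and a share d of them fails the joint definition. Complete responders = 16 × (1 - d).

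| d | Complete responders | Rate | Exact 95% CI |
|---|---|---|---|
| 0 | 16/40 | 40% | 0.249 to 0.567 |
| 12.5% | 14/40 | 35% | 0.206 to 0.517 |
| 25% | 12/40 | 30% | 0.166 to 0.465 |
| 50% | 8/40 | 20% | 0.091 to 0.357 |

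**5. Patients without an MRD marker, also under an assumption.** If a share u has no evaluable MRD marker and is counted as not complete, the highest attainable complete-response rate is 1 - u: 90%, 75% or 50% for u = 10%, 25% or 50%. If these patients are left out instead, n falls from 40 to 36, 30 or 20. The interval width near a rate of 0.4 then grows from 0.318 to 0.334 (14/36), 0.367 (12/30) or 0.448 (8/20). The protocol states neither u nor which handling applies.

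**The case against.** The trial is declared explorative, molecular response is a secondary endpoint analysed descriptively, and a stopping trigger may legitimately differ from an analysed endpoint. Handling of non-informative markers is often left to the statistical analysis plan. BCR-ABL can be read as included in MRD, because sections 2.2 and 3.1 speak only of MRD and mixed chimerism.

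Much of this stands and limits the weight of the point. It does not remove the contradiction. Section 11 equates complete response with molecular remission, section 3.1 stops at molecular remission, and section 8.1 stops at something else. An analysis plan cannot change when infusions stop. On BCR-ABL, the Synopsis describes MRD as Ig/TCR testing and lists BCR-ABL as its own item. Only an entry threshold (a ratio of at least 10^-4) is given, with no response cut, so the wording is at best ambiguous.

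Three stronger readings are tempting and are not supported.
- A reader might infer from the pilot series, "hematological malignancies (AML, n=7; ALL, n=6; CML, n=1", that about half of the patients will lack an MRD marker. That is a count of diagnoses, it includes no MDS, and it says nothing about marker availability. Section 2.2 plans Ig/TCR or BCR-ABL testing in leukemia patients, which includes AML. The gap is documented directly only for MDS.
- A reader might infer that those stopped for response and the complete responders are different patients. The two groups overlap.
- A reader might infer that response duration is measured from the section 8.1 event. Section 11 lists rate and duration under its own definitions, and patients stopped for response remain in the study with a year of follow-up and obligatory chimerism.

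**Conclusion.** The point holds as a contradiction between definitions, and it should be fixed. Following the stated rules gives more than one event that ends infusions for response, and a complete-response criterion that cannot be evaluated in some eligible patients: MDS patients, for whom no MRD assay is stated, and any other patient in whom MRD is not done. BCR-ABL entrants have no explicit stopping or response criterion.

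The effect is confined to the complete-response rate, the complete/partial split, treatment exposure and the timing of the end-of-infusion assessment. The fall from 40% to between 35% and 20% rests wholly on the assumed 16/40 and the assumed 12.5% to 50% discordance. It shows sensitivity and is not a forecast. The stated interval widths remain correct for the combined rate.

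**What to change.** In section 11, define complete molecular response by the markers that are informative for each patient. A patient without an MRD marker is then neither automatically a non-complete responder nor classified without a stated rule. Name BCR-ABL/ABL with an explicit response cut chosen by the sponsor. Report the complete-response rate overall and by qualifying marker.

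Reconcile the Synopsis (duration of participation and schedule legend) and sections 3, 3.1, 3.3, 8.1 and 11, and state how complete donor chimerism relates to MC below 1%. The event that ends infusions and the event analysed should either be the same or be explicitly distinguished. Which treatment rule applies is for the sponsor.

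The cost is one reworded definition, consistent wording of the stopping criterion and one additional table. The sample size does not change.
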